### Co-interventions

Reinforcement of the primary dressing is permitted as per standard clinical practice. In such cases the reinforcing dressing, and the reason/s for applying it, will be recorded. On occasion children, parents or other health care providers outside the hospital remove the dressing within the first week. Should this occur, the study dressing will be reapplied and reasons for the early removal will be documented.

Interventions at dressing change, such as debridement, cleansing or coverage with cling-film prior to review are permitted in all arms, reflecting a real-life approach. In the case of a suspected or diagnosed wound infection the wound may be treated with antimicrobial agents (povidone iodine and/or nanocrystalline silver dressings). Common definitions for superficial surgical site infections (SSI) are predicated on an incisional, rather than excisional wound [19] and their appropriateness for DSW infection is questionable. We have taken a clinical approach based on the definition of a superficial SSI. Diagnosis of wound infection in this trial is by agreement of the treating clinician and a second burns surgeon. Criteria used for defining wound infection are qualitative, and include purulent discharge from the DSW surface; serous or haemoserous discharge alone does not constitute infection. Inflammation extending beyond the margins of the DSW at dressing change is another criterion. A surface swab is inaccurate and has a long lead time, but will nonetheless be performed for a colony count as it may provide some quantitative data in support of the diagnosis. A positive swab alone does not constitute an infection. We do not perform punch biopsies of our patients in clinic. As part of the dressing protocol these wounds will all be photographed.

Standard analgesia will be provided to all children. For larger total body surface area (TBSA) wounds it is our practice to augment this with gabapentin and/or antihistamines in an effort to decrease itch. These medications are surgeon dependent. All medications will be recorded.

### Study outcomes

#### Primary endpoints

There are two primary endpoints: pain, and time to re-epithelialisation. Pain will be assessed at several time points. Firstly, at four hours following completion of the operation. This will allow measurement in day-case patients prior to their discharge. By taking these scores face to face we hope to facilitate the telephone call the following day. It is also an opportunity to clarify directly with parents that we are scoring DSW pain, rather than graft site pain. Secondly, at one day later via a telephone call, or following ward review for inpatients. Thirdly, immediately before premedication prior to removal of the DSW dressing in clinic. Premedication will be with oxycodone 0.1 mg/kg orally (Mundipharma Pty Ltd, Sydney, NSW 2000, Australia), and oral paracetamol 150 mg/kg (sanofi-aventis Australia Pty Ltd, Macquarie Park, NSW 2113, Australia). Fourthly, at two minutes following removal of the DSW dressing. The graft dressing will not be taken down until after these scores are recorded. If a dressing is reapplied, the recordings at time points two, three and four above will be repeated for each subsequent change.

A variety of scales will be used for assessing pain, determined by who is performing the assessment (observer, parent or child), and by the age of the child. The face, legs, activity, cry and consolability (FLACC) scale will be used by nursing staff [20]. Where children are old enough, the Revised Faces Pain Scale (FPS-R) will be used for patient self-reporting of pain [21]. We will collect FPS-R data for children aged from three years, recognising that data are sparse for children below the age of five years [21]. Parents will use an 11-point (0 to 10) numeric rating scale (NRS). This, rather than a visual analogue scale, was chosen to facilitate the accuracy of recording during a telephone call.

Re-epithelialisation is defined as over 95% wound healing and no requirement for further wound dressing. Scabs or crusts are defined as unhealed areas. This endpoint is doubly assessed. In the clinic the treating doctor assesses percentage re-epithelialisation. It is further assessed from digital photography by an independent surgeon blinded to the DSW dressing. Photographs will be taken at each dressing change and at each subsequent clinic visit for care. In the clinic a visual percentage re-epithelialisation will be requested. The blinded observer will subsequently mark out the edges of the wound, and any unhealed areas. Surface area computer mapping will then be used to determine percentage re-epithelialisation. We will test concordance between clinician assessment and computer mapping regarding re-epithelialisation.

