## Methods/Design

### Protocol and registration

This trial has approval from the Royal Children’s Hospital Human Research Ethics Committee (approval number: HREC/14/QRCH/36), and from the University of Queensland Medical Research Ethics Committee (approval number: 2014000447)*.* The methodology is specified in advance, documented in a protocol and has been registered prior to recruitment commencing (Australia and New Zealand Clinical Trials Register, identifier: ACTRN12614000380695) [14]. The methods are summarised here according to the revised Consolidated Standards for Reporting Trials (CONSORT) statement [15].

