### Eligibility criteria for patients

From recruitment commencement, all patients of the PLPBC requiring STSG will be consecutively considered for inclusion, until recruitment is completed. Our unit treats only pediatric patients, aged from birth to 15 years. Regardless of the predicted size of the DSW, all children undergoing STSG will be considered for inclusion.

Patients will be assessed for eligibility by their primary surgeon or an investigator. If eligible, they will be approached by a trained staff member not involved in their primary care. Parent or caregiver informed consent will be obtained and documented. Where appropriate, child assent will be documented (Additional files 1 and 2).

Exclusion criteria include non-English speaking parents or caregivers, as we will not be able to gather data the following day by telephone. Also excluded are children with a known cognitive impairment, and children under the care or investigation of the Department of Communities, Child Safety and Disability Services. Only thigh or buttock DSWs will be included.

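### The oral paracetamol premedication is printed as 150 mg/kg in one dose (1.5 g at 10 kg, 7.5 g at 50 kg), which is not credible for children and must be checked and corrected

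*Protocol article*

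**What the plan says.** The figure is in the protocol article, Methods/Design, Study outcomes, under Primary endpoints. Pain is one of two primary endpoints and is scored at four time points. The third is taken just before premedication: "Thirdly, immediately before premedication prior to removal of the DSW dressing in clinic". The regimen follows: "Premedication will be with oxycodone 0.1 mg/kg orally", then the manufacturer of the oxycodone, then "and oral paracetamol 150 mg/kg". The last score comes after the dressing is off: "Fourthly, at two minutes following removal of the DSW dressing".

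The cycle can recur: "If a dressing is reapplied, the recordings at time points two, three and four above will be repeated for each subsequent change". As the third time point is defined by premedication, the regimen may be given more than once to the same child.

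On the population, Eligibility criteria for patients says: "Our unit treats only pediatric patients, aged from birth to 15 years". On drug records, Co-interventions says: "All medications will be recorded". Protocol and registration reports ethics approval and says of the underlying document: "The methodology is specified in advance, documented in a protocol".

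**The concern.** A paracetamol dose of 150 mg for every kilogram, given by mouth at one time, runs to several grams in an older child and well over a gram in a toddler. That is not believable as routine preparation for a dressing change, and it reads like an extra zero or a lost decimal point.

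Two things are at stake. The first is safety. This is a per-kilogram dose for children, stated as what will be given in every arm. The Discussion hopes the protocol will be used again for future dressings, so a wrong figure could be carried forward. Data monitoring states that there is no data safety monitoring board; oversight rests on the unit's weekly team meeting and monthly morbidity meeting. The second, lesser matter is reporting. The premedication defines the analgesia under which the fourth pain score is taken. A reader who cannot trust the dose cannot say under what conditions that score was obtained, or reproduce them.

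**Working it through.** **Inputs**

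- Printed paracetamol dose: 150 mg/kg, oral (Primary endpoints).
- Age range: birth to 15 years (Eligibility criteria for patients).
- Body weights: not in the article. I assume 3 to 50 kg for illustration.

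The article does not derive the 150 mg/kg, so there is no calculation of its own to reproduce. The check is what the figure means when applied.

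**Formula:** dose in g = mg/kg × weight in kg ÷ 1,000.

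The last column assumes that one decimal place slipped (150 ÷ 10 = 15 mg/kg). It shows the possible size of the error and is not a proposed dose.

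| Weight (assumed) | As printed, 150 mg/kg | If one decimal place slipped, 15 mg/kg |
|---|---|---|
| 3 kg | 0.45 g | 0.045 g |
| 10 kg | 1.5 g | 0.15 g |
| 20 kg | 3.0 g | 0.30 g |
| 30 kg | 4.5 g | 0.45 g |
| 50 kg | 7.5 g | 0.75 g |

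Under that assumption the ratio is 150 ÷ 15 = 10 at every weight.

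**Does anything else in the article change the reading?**

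1. *A daily total?* No. The sentence describes medication given before one procedure and has no per-day qualifier.
2. *A cap?* None is stated. By contrast, Surgical procedure limits the topical bupivacaine to a weight-based safe maximum of 2 to 2.5 mg/kg.
3. *A second figure?* None. Co-interventions mentions standard analgesia without a dose.
4. *Damage in reading the PDF?* Unlikely. The sentence is intact, and the oxycodone figure of 0.1 mg/kg in the same sentence kept its decimal point.

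So the article contradicts neither itself nor the figure. It prints one implausible value and offers no means of settling the right one.

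**The case against.** The best case on the other side accepts the quotation and the multiplication and disputes the weight given to them.

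- **Nothing is miscalculated.** The figure has no derivation, and the article gives no reference dose. This stands as a matter of labelling: it is a dosing misprint rather than an arithmetic error. That the figure is implausible is elementary clinical knowledge and does not rest on a particular source. What the intended dose was is not known, and the 15 mg/kg column carries no weight beyond illustration.
- **Staff do not dose from a journal article.** The article summarises a separate protocol, and the trial is meant to mirror the unit's ordinary practice. Experienced staff would probably not follow the printed figure. This stands too: there is no evidence that any participant was exposed. It lowers the likelihood of harm but does not make the published dose right.
- **The trial's inference is untouched.** Premedication is the same in every arm and follows the third pain score. Sample size, randomisation and analysis are unaffected. This is correct, and the point is not put forward as a threat to the comparison.
- **The remedy assumes what the sources contain.** The article does not say that the approved protocol states a paracetamol dose, nor that the medication records hold doses as well as drug names. This is fair. It is why the check should include the unit's premedication order and why each later step depends on what the check shows.

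None of these objections rescues 150 mg/kg as a single oral dose for a child.

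**Conclusion.** The point holds. The printed dose is wrong on its face: 1.5 g at 10 kg, 3.0 g at 20 kg and 7.5 g at 50 kg, by mouth, in one administration, possibly repeated at later dressing changes. The gram amounts rest on illustrative weights; the per-kilogram figure does not. That it is ten times too high is an assumption about how the slip arose, and the article cannot confirm it.

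The correction is obligatory on safety grounds, because this is a stated drug dose for children and the cost of putting it right is trivial. It is no evidence that any child was overdosed, and it gives no reason to doubt the comparison between dressings.

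**What to change.** 1. Check the paracetamol figure against the ethics-approved protocol and the unit's premedication order.
2. If the confirmed figure differs from the printed one, publish an erratum so that the sentence gives oral oxycodone 0.1 mg/kg and oral paracetamol at [figure confirmed from the approved protocol and the premedication order] mg/kg. No value should be inserted from inference.
3. If the approved protocol itself reads 150 mg/kg, amend it as well, and do so at once.
4. Use the trial's medication records, so far as they hold doses, to establish what was given. Trial status reports 34 children already grafted and randomised by 1 August 2014, so there are records to look at. Report deviations only if they show that the printed dose was used.

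The cost is a one-line erratum and a look at records the trial already keeps. If step 3 applies, add a protocol amendment. No patients, visits, procedures or analyses are added.

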#### Secondary endpoints

Itch is a secondary endpoint. The Itch Man Scale will be used for assessing itch. This scale has been validated in children [22]. These assessments will occur at the same time as the pain scores above. Itch will also be assessed at the three, six and 12 month reviews. DSW appearance at three, six and 12 months is a secondary endpoint. This will be assessed in a number of ways: ultrasound measurement of scar thickness; digital three-dimensional photography and edge marking to determine computer-mapped areas of scarring. This will be compared with previous digital images; Patient and Observer Scar Assessment Scale (POSAS) [23]. We chose POSAS as this has superior performance in a systematic review over other scar assessment scales, and from a pragmatic viewpoint is the scale PLPBC staff are most familiar with [24]. It also seeks the opinions of the patient regarding their scar, something we consider important. In practice for many of our young children we use the parent opinion. Where possible we ask both parent and patient. There are some reliability data supporting the use of this scale in children above the age of six years [25]. Below this age caregiver opinion will be sought as a proxy for the child.

Ease of dressing application and removal is a secondary endpoint. Setup time will not be recorded; times for removal and reapplication of dressing will be recorded. A numeric rating scale (0 to four) will be used to ascertain opinions regarding ease of dressing removal at first change. Ease of dressing measurements in theatre are confounded by lack of blinding, and by the variable nature and size of the areas to be dressed. Ease of dressing scores in clinic will focus primarily on the ease with which the primary dressing is removed from the skin surface.

Cost is a secondary endpoint. This will be assessed using hospital pricing for the dressings used, and nursing time for dressing changes. Additional visits, where required, will also be included in the cost analysis. Routine visits will not be costed, since these are a standard part of treatment. Any additional treatments outside of standard care, such as treatment for infection, will be included in costing. A cost-utility analysis will not be performed, as the site and nature of the burn wound grafted will confound quality of life results. We will thus not be able to isolate the DSW from the grafted site in order to perform cost-utility on the DSW alone.

### Randomisation

Randomisation will occur in the operating theatre, immediately prior to application of the DSW dressing. We have used unrestricted randomisation, generated using an online program (http://stattrek.com/) [26]. Randomisation of participants will continue until each of the study groups has a minimum of 28 participants reaching the primary endpoints. Allocation concealment will be via the use of sequentially numbered, sealed opaque envelopes pre-prepared by a third party.

Patients will be recruited into the trial when a decision to graft is made following review of the burn injury. The patient will be randomised intra-operatively, further separating recruitment and consent from randomisation.

### Blinding

The nature of the study mitigates against full blinding, but some assessments can be blinded. Secondary dressings for all patients are the same, so clinic staff will not initially know which arm the patient is in. Clinic staff, patients and parents are blinded for assessments of pain and itch until the first dressing change. Following that point, blinding is not possible for the remainder of the pain and itch assessments as the dressing will have been revealed.

One of the assessors of re-epithelialisation will be blinded, as these assessments will take place using digital photography. Details of the dressing will not be made available to this assessor. Where there is discrepancy between these two observations, the blinded assessor will be taken as the definitive assessment in an effort to overcome performance bias. The assessments of scar appearance will also be blinded, as assessors will have no knowledge of the dressing used.

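### The blinding claim for scar appearance cannot be relied on for the patient/parent part of the POSAS, because the dressing has been revealed to those raters before they score

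*Protocol article*

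**What the plan says.** All references are to the protocol article.

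- **Blinding**, on scar outcomes: "The assessments of scar appearance will also be blinded, as assessors will have no knowledge of the dressing used". No scar measure is exempted.
- **Secondary endpoints**: "DSW appearance at three, six and 12 months is a secondary endpoint". It is measured by ultrasound thickness, by computer-mapped area from three-dimensional photographs, and by the POSAS.
- **Secondary endpoints**, on the POSAS: "It also seeks the opinions of the patient regarding their scar, something we consider important". On who gives that opinion: "In practice for many of our young children we use the parent opinion. Where possible we ask both parent and patient". For children under six: "Below this age caregiver opinion will be sought as a proxy for the child".
- **Blinding**, on families and clinic staff: they are blinded for pain and itch up to the first dressing change. After it, "blinding is not possible for the remainder of the pain and itch assessments as the dressing will have been revealed".
- **Wound treatment**: the first dressing change takes place in clinic on day 7.

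**The concern.** The scar sentence gives a reason for the blinding: the raters do not know which dressing was used. Under the plan, some of those raters are the children and their parents. The preceding paragraph of the same section says that blinding of these people, for the outcomes they report there, ends when the dressing is exposed. The plan thus claims a property for the scar outcome that one of its components cannot be assumed to have.

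Scarring is among the criteria in the trial's question (Background), and the best-performing dressing is to become the centre's standard. The Discussion also presents blinded assessment as a feature of the design. A reader who takes the sentence at face value would give a difference on the patient/parent scale the weight of a blinded finding, although expectation or the experience of the dressing removal could have contributed to it.

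**Working it through.** **Step 1: the text, side by side.** This is a question of consistency, so the main check is a reading.

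| Question | Answer | Section |
|---|---|---|
| Which scar assessments are said to be blinded? | All, without exception | Blinding |
| Is a patient or parent rating one of them? | Yes, through the POSAS | Secondary endpoints |
| When is it taken? | 3, 6 and 12 months | Secondary endpoints |
| When is the dressing revealed to families? | At the first dressing change | Blinding |
| When is that? | Day 7 | Wound treatment |

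Three months is about 91 days, and 91 − 7 = 84 days. The dressing is therefore revealed about 12 weeks before the earliest scar rating.

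**Step 2: a check against itch.** Itch is also assessed at the three, six and 12 month reviews (Secondary endpoints), and the Blinding section concedes that itch after the first change is unblinded. At those visits the plan therefore treats itch as unblinded and scar appearance as blinded, although families rate the latter too. Nothing in the article explains the difference.

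**Step 3: does the sample size change?** The plan's own figure reproduces. For one pairwise comparison by the normal approximation,

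n = 2 (z₀.₉₇₅ + z₀.₈₀)² SD² / Δ²

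With Δ = 3 days, SD = 4 days, two-sided α = 0.05 and 80% power, n = 2 (1.960 + 0.842)² × 16 / 9 = 27.9, rounded up to 28, as stated. For pain (Δ = 2, SD = 2.5), n = 24.5, rounded up to 25, so 28 suffices. Neither calculation uses a scar outcome, so both stand.

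**Step 4: an illustration of size.** The documents give no bias for the patient/parent scale. Assume no true difference between two arms and a pure rating shift of b SD in one of them. With n = 28 per arm, the two-sided two-sample t-test has 54 degrees of freedom, critical value 2.005 and noncentrality b√(n/2) = b√14.

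| Assumed shift b (SD) | Noncentrality | Chance of P < 0.05 |
|---|---|---|
| 0 | 0 | 5.0% |
| 0.1 | 0.37 | 6.6% |
| 0.2 | 0.75 | 11.4% |
| 0.3 | 1.12 | 19.7% |
| 0.5 | 1.87 | 45.1% |

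The shifts are assumptions. The 28 is the minimum per arm with primary outcome data; the number rated at the scar visits is not stated.

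**The case against.** The best defence is that the word assessors means third-party raters. The Blinding section names clinic staff, patients and parents when it discusses pain and itch. It then uses assessor for the people judging re-epithelialisation, and the scar sentence follows directly. The section also opens by saying that only some assessments can be blinded. This reading would rescue the reason given in the sentence, but not its main clause, which covers scar appearance assessment as a whole. For re-epithelialisation the section takes care to say that only one of the two assessors is blinded; for scar it sets no such limit.

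Other parts of the defence stand and limit the point:

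- A reader might infer that every child's rating is unblinded. The article does not say that. Its explicit statement on loss of blinding concerns pain and itch. All wounds receive the same follow-on dressing from day 7, and the article does not say whether families are told the product or would recall it months later. Knowledge of the dressing is likely but not established for each family.
- A reader might infer that the observer part of the POSAS is safely blinded. The article does not identify its rater, it describes the scale as the one the centre's staff know best, and clinic staff lose their blinding at the same dressing change.
- A reader might take the 11% to 45% range as the trial's actual error rate. The documents supply no bias size. All three dressings are in current use and equipoise is stated, so there is no evident reason for families to favour a particular arm.
- A reader might suppose that the two POSAS parts will be added into one total. The article proposes no such total.

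**Conclusion.** The point holds in a limited form. The Blinding section's sentence on scar appearance is broader than the design supports: for the patient/parent part of the POSAS at three, six and 12 months, blinding cannot be relied on. This follows from the article's own statements and needs no assumption about what families remember, because the plan claims that raters have no knowledge of the dressing and offers no basis for that claim where families are concerned.

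The reach is one component of one secondary endpoint. Ultrasound thickness and mapped area can still be blinded. So can the observer scale, on condition that its rater is kept unaware of the dressing. The primary endpoints and the sample size are not touched. The effect on error rates is not quantifiable from the documents; the table above shows only that it could range from negligible to substantial, depending on an assumed shift.

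**What to change.** 1. Reword the scar sentence in the Blinding section so that it covers only measures whose rater is kept unaware of the dressing: ultrasound thickness, computer-mapped area, and the POSAS observer scale if its rater did not attend the dressing changes.
2. Say who rates the observer scale. If that person may have attended a dressing change, do not call the scale blinded.
3. Describe the POSAS patient/parent scale as an unblinded, patient-reported measure, and report it separately from the observer scale.
4. Rest any scar conclusion described as blinded on the measures in item 1.

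This is a change of wording. It needs no new data or visits; the one practical demand is to choose an observer-scale rater who was absent from the dressing changes, if that scale is to count as blinded. The cost is that the patient/parent scale, which the investigators value, carries somewhat less weight in the scar conclusion.
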